**Method:**

Fifty-four patients aged 40 years and above with obstructive, restrictive or mixed respiratory impairments attending the respiratory clinic at the Lagos State University Teaching Hospital, Ikeja (LASUTH), will be recruited and assigned to three groups of 18 participants based on the class of respiratory impairment. Participants in each category of respiratory impairment will be subdivided into three groups. A final group of six participants per class of impairment will participate in the experiment. Our study will be a double-blind, randomised control trial with two intervention groups and one parallel placebo control group. Pulmonary function will be assessed before and after every procedure while the six-minute walk test (6MWT), Medical Research Council dyspnoea scale and the Pulmonary Functional Status and Dyspnea Questionnaire-Modified will be assessed fortnightly during our study. Data will be analysed using descriptive and inferential statistics and a repeated MANOVA; *p* < 0.05.

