### Procedure

#### Randomisation and blinding

The patients attending the respiratory clinic of LASUTH, Ikeja, Lagos, Nigeria, West Africa, will be approached for possible interest in participating in our study. A bulk text message captioned ‘Invitation to a study on respiratory impairments’ will be circulated to interested participants using a Luxury bulk SMS platform.

Interested potential participants will be screened by Examiner 1 (the study physician) using the inclusion and exclusion criteria to determine their suitability. If suitable, they will be assigned to three groups of 18 participants per group based on the class of respiratory impairment by research assistant 1 (RA1). A simple random sampling technique will be used to assign interested participants into three major groups (groups A, B and C): subgroup A (x, y, z), subgroup B (e, f, g) and subgroup C (h, i, j). The allocation will be performed in phases through balloting according to the class of respiratory impairment, with each participant picking a slip of paper in a ballot box containing equal pieces marked either ‘A’ ‘B’ or ‘C’ for the main group, ‘x’ ‘y’ or ‘z’ for subgroup A, ‘e’ ‘f’ or ‘g’ for subgroup B and ‘h’ ‘i’ or ‘j’ for subgroup C, based on the number of participants present (Figure 2). The first author, who is the principal investigator (PI) will generate the ballot slip, while research assistant 2 (RA2) will supervise the balloting. There will be pre-commencement training for the field workers involved in the randomisation, investigation and data collection.

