Following successful allocation to one of the three groups, the participants will be required to breathe in the upright sitting position before commencing the exercise using the most convenient respiration method. A volume-incentive spirometer (Coach 2 device), which enables the patient to inhale air through a mouthpiece and corrugated tubing attached to plastic bellows, will be used for the inspiratory exercise, with the volume of air displaced indicated on a scale located on the device enclosure (Kumar et al. 2016). The procedure will be demonstrated to the participant to ensure that it is well understood before commencement. After the participants have achieved the maximum volume, they will be instructed to hold the volume of air attained on the scale constant for 3–5 sec before exhalation (Zayed, Ahmed & Salem 2017). The participants will repeat the exercise three times to complete one set; three sets will be performed up to a maximum of 10 attempts. One minute of rest will be given between sets to reduce fatigue. The participants will leave after the following musculoskeletal assessment: The musculoskeletal assessment will involve screening of the participants’ musculoskeletal system for possible pain, swelling or limitation in joint range of motion. The procedure will be stopped whenever the subject feels dizziness or experience pain in the chest. The procedure will be repeated three times a week for 12 weeks. The MRC dyspnoea scale, 6MWT and PFSDQ-M will be conducted fortnightly during the study period.

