### Control group

Placebo effect refers to treatment that is essentially not therapeutically effective (Rossettini et al. 2020).

Following successful allocation, participants will be required to breathe in the upright sitting position using a respiration method that is most convenient for them. An assessment of the participants’ musculoskeletal system will be conducted as a placebo immediately after their pulmonary function test is conducted. The musculoskeletal assessment will involve a medical screening of the participants’ musculoskeletal system for possible pain, swelling or limitation in joint range of motion. The participant will leave after the musculoskeletal examination. The procedure will be repeated three times a week for 12 weeks. The MRC dyspnoea scale, 6MWT and PFSDQ-M will be conducted fortnightly during our study period.

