### Medical Research Council dyspnoea scale

The MRC breathlessness scale quantifies the disability associated with breathlessness by identifying if breathlessness occurs when it should not (Grades 1 and 2) or by quantifying the associated exercise limitation (Grades 3–5) (Stenton 2008). Mahler and Wells (1988) reported a 98% agreement between observers recording MRC breathlessness scores. In a statement by the ATS, the score correlates well with the results of other breathlessness scales, lung function measurements and direct measures of disability such as walking distance (stats.oarc.ucla.edu). The MRC breathlessness scale is commonly used to describe patient cohorts and stratify them for pulmonary rehabilitation interventions, predict survival and use as complementary to FEV_1_ in describing disability in those with COPD and other forms of respiratory impairments (Bestall et al. 1999; Nishimura et al. 2002; Wedzicha et al. 1998).

The instrument has five statements that describe the range of respiratory disability. Depending on the literacy of the participants, the instrument can either be self or interviewer administered; RA2 will explain the content of the instrument to the participants prior to its administration. Participants will be encouraged to clarify issues related to the instruments before submitting their responses. The instrument will be administered at our study site at 2 week intervals during the study period. They will be comfortably seated on a chair without wheels, and the research instrument and writing materials placed on a desk. The RA2 will carefully introduce the research instrument to the participants, explain the domains and indicate the options stated on the instruments. Respondents will be informed to seek clarification on the instruments whenever required from either the PI or RA2, both blinded to group allocation.

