### Data analysis

The Statistical Package for Social Sciences (SPSS Inc, Chicago, Illinois, United Sates) version 26.0 for windows package programme will be used to analyse data. Descriptive statistics of mean, standard deviation, frequencies and percentages will be used to summarise the results. Bar charts, pie charts and histograms will be utilised for pictorial illustration. A multivariate analysis of variance (MANOVA) will be used to compare the outcome pulmonary function variables (FEV_1_, FVC, FEV_1_/FVC, PEFR) and QoL (6MWT, MRC dyspnoea scale score and PFSDQ-M score) among groups, while the Bonforreni’s *t*-test will be utilised for post hoc analysis to detect where significant changes occurred in the outcome variables. Dependent t-tests will be used to compare the pre- and post-test results within variables while independent t-tests will be used to compare the outcome variable among the study and control groups. The level of significance will be set at *p* ≤ 0.05.

The study does not potentially involve risk or harm, as all interventions can only be performed within the limit of the patient’s tolerance. However, participants may experience mild discomfort because of the exercise, including temporary muscle soreness, increased heart rate, blood pressure, sweating and dizziness. All necessary care will be in place to prevent the occurrence of any adverse event. However, in case of a report of serious adverse events (e.g. comorbidities, injuries, persistent excruciating pain, dizzy spells, headache, etc.) after the intervention or at any point during the trial, we would consider unblinding the participant to the intervention for their safety. Additionally, the participants will be instructed to report adverse events to the first author PI or the physiotherapist supervising their group. To ensure adequate supervision, participants per group to be attended in a day will be limited to a maximum of three. Arrangements will be made with the Accident and Emergency units of the research site to provide a standby medical team. The University of KwaZulu-Natal insurance scheme on clinical trials has fully covered participants in this type of study.

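### The assistant who supervises the ballot is also declared blinded for the MRC scale and PFSDQ-M, and participants cannot be blind to their procedure, so the double-blind, placebo label does not describe this trial

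*Protocol article*

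**What the plan says.** The abstract (Method) states: "Our study will be a double-blind, randomised control trial with two intervention groups and one parallel placebo control group". The Study Design section keeps the placebo control but does not repeat the blinding claim.

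**Allocation.** Under Randomisation and blinding, groups are set by lot, "with each participant picking a slip of paper in a ballot box containing equal pieces marked either" one of several letters. On who does what: "The first author, who is the principal investigator (PI) will generate the ballot slip", while "research assistant 2 (RA2) will supervise the balloting". Research assistant 1 (RA1) sorts participants by class of impairment and is given no outcome role anywhere.

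**Assessment.** For the MRC scale, RA2 introduces and explains the instrument, and participants may seek clarification "from either the PI or RA2, both blinded to group allocation". The PFSDQ-M section repeats this arrangement. The Six-minute walk test section has the principal investigator (PI) supervise the walk, also as a blinded person. The Spirometry section gives lung function testing to a separate certified technician, declared blinded, with no stated part in allocation.

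**Treatment.** One arm inhales through a volume-oriented device, one blows into a peak flow meter, and in the control arm an assessment of the "musculoskeletal system will be conducted as a placebo immediately after their pulmonary function test is conducted". The two training arms receive the same screen; in the inspiratory arm, for example, "The participants will leave after the following musculoskeletal assessment".

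**Safety.** The Data analysis section says "participants will be instructed to report adverse events to the first author PI or the physiotherapist supervising their group". It also allows for breaking a participant's blind after a serious adverse event.

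**The concern.** Group allocation is exactly what the ballot decides. A person who oversees the draw cannot be assumed ignorant of its result when explaining a subjective questionnaire to the same participants every fortnight. Participants, for their part, know which procedure they carry out.

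The MRC scale and PFSDQ-M are subjective, and the walk test depends on effort. All three appear in both specific objectives and in the planned MANOVA. The stated purpose is to find the more suitable technique for each impairment with six participants per cell, so a few influenced scores could matter. A report that repeats the double-blind, placebo description would also credit the trial with a protection it does not have.

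**Working it through.** No alpha, power or sample-size figure depends on this point, so the check is a comparison of roles and procedures across sections.

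**1. Who has an allocation role and who is called blinded**

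| Person | Part in allocation | Part in outcomes | Declared blinded? | Conflict |
|---|---|---|---|---|
| RA1 | Sorts by impairment class | None stated | Not stated | None |
| RA2 | Supervises the ballot | Introduces and explains MRC and PFSDQ-M | Yes | Direct, unless the letter key is withheld |
| PI | Generates the slips; may receive adverse-event reports | Supervises 6MWT; answers MRC and PFSDQ-M queries | Yes | Present, but weaker |
| Spirometry technician | None stated | Primary outcome | Yes | None |

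**2. RA2.** The slips carry letters, not treatment names. RA2's two roles can coexist only if RA2 sees letters and never learns what they stand for. The article describes no such arrangement. A letter code would also be fragile: 54 participants over 3 × 3 = 9 subgroups gives 54 / 9 = 6 people sharing each subgroup letter, so one remark about a device could unmask all six to anyone who knows their letters. RA2 meets participants fortnightly, which over 12 weeks is about 12 / 2 = 6 occasions each, and is one of two people they are told to ask for help.

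**3. The PI.** Making the slips suggests knowledge of what the letters mean, but not of who drew which. Adverse-event reports could supply the missing link for some participants. They may instead go to the group's physiotherapist, so this exposure is possible, not certain.

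**4. Participants.** Each attends 3 × 12 = 36 sessions and performs one of three visibly different routines: inhaling through the inspiratory device, exhaling into a peak flow meter, or the musculoskeletal screen without a training device. No sham device is described. Both training arms also receive the screen, so it is common to all arms and imitates neither treatment. The sample size section itself labels the third level of the therapy factor as no therapy. Participants cannot be blind to the procedure, yet the safety text treats them as people whose blind could be broken.

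**5. Outcomes touched.** Of the outcomes other than spirometry, the MRC scale and PFSDQ-M involve both RA2 and the PI, and the 6MWT involves the PI. That is three of three. Spirometry has an assessor whose blinding nothing in the text contradicts.

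**The case against.** The strongest defence is that RA2's knowledge of treatment is inferred. Supervising a ballot is not the same as reading or recording every slip, the slips bear only letters, the flow diagram is not shown, and an article may leave concealment detail to the full protocol. This stands in part: it turns a flat falsehood about RA2 into a conflict that a withheld key could resolve. It does not remove the conflict, since the article asserts both roles without reconciling them, and it does nothing for participants.

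A reader might also infer more than the documents support:

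- *That neither side of the double blind holds.* Lung function is the primary outcome, and its technician is separate and declared blinded. That assessor's blinding is not in question.
- *That RA2 interviews participants on both questionnaires.* Interviewer administration is mentioned only for the MRC scale, depending on literacy, and RA2 is not named as the interviewer. For the PFSDQ-M, RA2 introduces and explains.
- *That the PI is certainly unblinded.* Neither slip-making nor the optional adverse-event route establishes this. The discomforts listed do not separate the two training arms, though they might suggest exercise rather than control.
- *That controls use no device at all.* The control screen follows a lung function test, so they blow into a spirometer. What they lack is a training device.
- *That all 54 participants' scores will be biased.* The text shows an opportunity for bias, not its occurrence.

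Finally, participant blinding is rarely feasible with device training. That is fair, and it makes this part of the point a matter of labelling and interpretation, not a fault in choosing the comparator.

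**Conclusion.** The point holds in three parts of differing strength.

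1. **Participants: firm.** They cannot be blind to the procedure they perform. The double-blind and placebo wording in the abstract, and the safety text about breaking a participant's blind, are wrong as written. A participant might be kept unaware of the study hypothesis, but the article does not say so and that would not justify the label.
2. **RA2: firm as a contradiction in the text.** Ballot supervision and declared blinding are incompatible unless the letter key is withheld. That RA2 actually knows the treatments is a strong inference, not a stated fact.
3. **PI: weaker.** Blinding for the 6MWT, MRC scale and PFSDQ-M is undermined by making the slips and by possible adverse-event reports, without being plainly contradicted.

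The reach is all three non-spirometry outcomes in all 54 planned participants. The size of any bias cannot be derived from the document, and assessor blinding of the primary outcome is unaffected.

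**What to change.** - **Separate the roles within existing staff.** RA1 prepares the slips, supervises the ballot, and holds the letter key and allocation log. RA2 and the PI then have no part in allocation. State this under Randomisation and blinding.
- **Reconcile the adverse-event text with the PI's claimed blinding.** The Data analysis and Six-minute walk test sections need to agree. How reports should be routed is a safety decision for the investigators and is not proposed here.
- **Correct the label.** Replace double-blind with placebo control by: outcome-assessor-blinded, participants not blinded, control without a training device. This is supportable only once the two changes above are made. Amend the safety sentence on breaking a participant's blind to match.
- **State the interpretation in advance.** Read MRC and PFSDQ-M contrasts against control as open-label self-reports.

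The cost is a transfer of tasks and some rewording, with no added staff, participants or analyses. The downside is a less favourable design label.

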**FIGURE 2 F0002:**
[figure not shown]
Consort flow diagram for recruitment and randomisation of participants.

## Description of equipment, procedure and outcome measures

### Inspiratory incentive spirometry

Evidence from a Medline search from 1952 to 2008, EMBASE search from 1980 to 2008 and CINAHL search from 1980 to 2008 using OVID interface and Cochrane library search revealed several articles with incentive spirometry as a reliable tool for lung expansion in the postoperative physiotherapy rehabilitation of chest conditions (Agostini & Singh 2009).

Different types of incentive spirometer are available in the market; the volume-oriented incentive spirometer designed to improve lung volume has a visible scale that monitors the inspiratory effort of the patients (Agostini & Singh 2009). Mediflo Duo (Mediflex, Hamburg, Germany), Mediciser (Eastern Medikit Ltd., Gurgaon, India), Coach 2 Device (MediMark Europe, Grenoble, France), Spiroball (Leventon, Barcelonia, Spain) and several others are brands of incentive spirometry for inspiratory, volume-oriented respiratory exercises (Agostini & Singh 2009).

Following successful allocation to one of the three groups, the participants will be required to breathe in the upright sitting position before commencing the exercise using the most convenient respiration method. A volume-incentive spirometer (Coach 2 device), which enables the patient to inhale air through a mouthpiece and corrugated tubing attached to plastic bellows, will be used for the inspiratory exercise, with the volume of air displaced indicated on a scale located on the device enclosure (Kumar et al. 2016). The procedure will be demonstrated to the participant to ensure that it is well understood before commencement. After the participants have achieved the maximum volume, they will be instructed to hold the volume of air attained on the scale constant for 3–5 sec before exhalation (Zayed, Ahmed & Salem 2017). The participants will repeat the exercise three times to complete one set; three sets will be performed up to a maximum of 10 attempts. One minute of rest will be given between sets to reduce fatigue. The participants will leave after the following musculoskeletal assessment: The musculoskeletal assessment will involve screening of the participants’ musculoskeletal system for possible pain, swelling or limitation in joint range of motion. The procedure will be stopped whenever the subject feels dizziness or experience pain in the chest. The procedure will be repeated three times a week for 12 weeks. The MRC dyspnoea scale, 6MWT and PFSDQ-M will be conducted fortnightly during the study period.

### Expiratory incentive spirometry

Peak flow meters are portable hand-held device designed to measure how fast an individual can blow out air from the lungs during forceful exhalation, the peak flow meter evaluates airflow through the airways and monitors the degree of airway obstruction (Adeniy & Saminu 2011). The low range peak flow meter and the standard range peak flow meter are the two major types of peak flow meters; the low range is specific for children between 4 and 9 years and adults with severely impaired lung function, while the standard type of peak flow meter is used for older children, teenagers and adults (Adeniyi & Saminu 2011)

In a double-blind study by Nazir et al. (2005), on the accuracy of peak flow meters, a strong positive correlation was found in the comparison of three peak flow meters A, B and C with Pearson’s product moment correlation coefficient (r) = 0.962 for product A versus B, (r) = 0.969 for B versus C and (r) = 0.961 for A versus C. However, the disagreement between the Bland and Altman plot indicates that the peak flow meter should not be interchanged in clinical practice in order to maintain its accuracy and reliability.

Following successful allocation, the participants will be required to breathe in the upright sitting position before commencing the exercise using the most convenient respiration method. In an upright sitting position, the participants will be asked to breathe in air through the nose to the maximum, then breathe out into a standard peak flow meter. The peak flow cursor will be adjusted to zero, and participants will be instructed to avoid touching the cursor during the exercise. The procedure will be demonstrated to the participants to ensure that it is well understood before commencement. They will be required to wrap their mouth tightly around the mouthpiece of the peak flow meter, to prevent the slippage of air around the corners of the device, then breathe out maximally into the peak flow meter as hard and as fast as possible (Adeniyi & Erhabor 2011). The effort will be noticed on the cursor. The cursor will be returned to zero, and the exercise will be repeated three times to complete one set. A total of three sets will be performed up to a maximum of 10 attempts. One minute of rest will be given between sets to reduce muscular fatigue. The procedure will be stopped if the participant feels dizziness or experiences pain in the chest. To avoid a Valsalva manoeuvre, participants will be asked not to hold their breath for more than 5 seconds following the maximum expiration. The participant will leave after the following musculoskeletal assessment. The musculoskeletal assessment will involve screening of the participants’ musculoskeletal system for possible pain, swelling or limitation in joint range of motion. The procedure will be repeated three times a week for 12 weeks. The participants MRC dyspnoea scale, 6MWT and PFSDQ-M will be conducted fortnightly during the study period.

